**Figure 3 figure3:**
[figure not shown]
Mediation Model of Insomnia Severity Improvements mediating the change in well-being associated with the intervention.

Statistical analyses aim 3 is to determine whether risk factors for insomnia that are aggravated during the COVID-19 pandemic predict worse insomnia and well-being outcomes at follow-up.

Hypothesis 3 is that high levels of social isolation, perceived stress, sleep reactivity, and screen time and low levels of physical activity caused by the COVID-19 pandemic will collectively predict a worse long-term outcome across both intervention arms. Two separate linear mixed models will be conducted for each outcome variable (insomnia severity and depressive symptoms). In each model, the outcome variable at 12 weeks and 28 weeks will be entered as the dependent variable with social isolation, perceived stress, sleep reactivity, screen time, and physical activity measures at baseline as well as experimental arm entered as predictors.

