### Objectives

Our feasibility, pilot study investigates the viability of an early treatment for insomnia symptoms to treat insomnia symptoms arising during the COVID-19 pandemic and determine pandemic-related risk factors for worsening well-being and sleep outcomes. We also assess the impact of the intervention on insomnia severity and well-being across 28 weeks.

We will accomplish these objectives by conducting a waitlist-controlled trial across 28 weeks to address 3 aims.

Aim 1 is to determine whether a brief, telehealth CBT-I reduces insomnia symptoms arising during the COVID-19 pandemic. We hypothesize that CBT-I will lead to improvements in insomnia severity, as measured by the Insomnia Severity Index (ISI) [35,36], across 28 weeks. We also hypothesize that fewer participants in the CBT-I group will meet the Diagnostic and Statistical Manual of Mental Disorders 5th Edition (DSM-5) criteria for insomnia disorder, compared with the waitlist control group at weeks 12 and 28.

Aim 2 is to determine whether brief, telehealth CBT-I mitigates negative mental health outcomes arising during the COVID-19 pandemic. We hypothesize that, compared with the waitlist control group, the CBT-I group will have an improved trajectory of well-being across 28 weeks and will have better well-being at weeks 7, 12, and 28. Additionally, we hypothesize improvements in insomnia symptoms will mediate improvements in well-being from baseline to weeks 6, 12, and 28.

Aim 3 is to determine whether risk factors for insomnia that might be aggravated during the COVID-19 pandemic predict worse insomnia and negative mental health outcomes at follow-up. We hypothesize that self-reported high levels of social isolation, perceived stress, sleep reactivity, and screen time and low physical activity at baseline will predict worse long-term outcomes at 12 and 28 weeks across both study groups.

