#### Primary Outcomes

Primary outcomes of insomnia, well-being, and predictors of treatment response are collected at baseline (week 0), weeks 6, 12, 28, and 56. Primary outcomes of insomnia (ISI) and well-being were also collected at weeks 1-5. The primary time points are weeks 6, 12, and 28.

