##### Predictors of Treatment Response

Baseline levels of sleep reactivity and pandemic-related risk factors, including loneliness, perceived stress, screen time, social connection, and physical activity, are measured as predictors of long-term treatment outcomes.

Loneliness is measured using the University of California, Los Angeles (UCLA) Loneliness Scale [49]. This self-report measure assesses participant's subjective feelings of loneliness and social isolation. The UCLA Loneliness Scale asks participants to rate how often each of the 20 items is descriptive of them, rated from 1 (never) to 4 (often). The responses are for an overall score range of 20 to 80, with higher scores indicating greater degrees of reported loneliness.

Sleep reactivity is measured by the Ford Insomnia Response to Stress Test (FIRST) [50]. This 9-item self-report tool measures risk of participants experiencing situational insomnia due to common stressful conditions. A higher score on the FIRST indicates higher sleep reactivity. The FIRST has good reliability and validity and has demonstrated high internal consistency across multiple demographic groups in clinical and population-based samples [51].

Perceived stress is measured using the Perceived Stress Scale (PSS) [52]. The PSS is a widely used 14-item self-report questionnaire that assesses how stressful participants believe their lives to be. Items are generalized and measure the degree to which participants judge their lives to have been uncontrollable and unpredictable over the course of the previous month. Items are scored on a 5-point Likert scale, with total scores ranging from 0 to 56 and higher scores indicating higher levels of perceived stress.

Screen time is measured through modified self-report questions in the Coronavirus Health Impact Survey (CRISIS) [53]. Participants are asked to estimate the number of hours spent per day, over the course of the 2 most recent weeks, watching television or digital media (eg. Netflix, YouTube, web surfing) or using social media (eg. FaceTime, Facebook, Instagram, Snapchat, Twitter, TikTok).

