#### Primary Analyses

Statistical analyses aim 1 is to determine whether a brief, telehealth CBT-I reduces insomnia symptoms arising during the COVID-19 pandemic. All primary analyses will be performed using the intention-to-treat principle. We will test whether CBT-I is superior to a waitlist control in reducing insomnia symptoms by using a mixed effects linear model with autoregressive error structure using intention-to-treat analysis with outcomes at time points 6, 12, and 28. Insomnia severity as measured by the ISI will be entered as the dependent variable with randomization group (2 levels), time point (weeks 0, 6, 12, and 28), and group-by-time interaction included as fixed effects. The model will also include a random slope. Several hypotheses (1.1a-d) will be tested using the described mixed effects model.

Hypothesis 1.1a is that individuals assigned to the CBT-I group will experience an improved trajectory of insomnia symptoms during the waitlist-controlled 28-week period relative to those assigned to the waitlist control group. This hypothesis will be tested using a likelihood ratio test of the coefficients of the time and group-by-time interaction of the aforementioned mixed effects linear model.

Hypotheses 1.1b-1.1d are that individuals assigned to the CBT-I group during the waitlist-controlled period will have lower insomnia symptoms compared with those assigned to the waitlist-control group immediately posttreatment (hypothesis 1.1b; week 6) and at the short-term (hypothesis 1.1c; week 12) and long-term (hypothesis 1.1d; week 28) follow-ups. These hypotheses will be tested using the aforementioned mixed effects linear model with independent likelihood ratio tests using the treatment coefficient for the posttreatment (hypothesis 1.1b; Δ_1_ in Figure 2), short-term (hypothesis 1.1c; Δ_2_ in Figure 2), and long-term (hypothesis 1.1c; Δ_3_ in Figure 2) follow-up time points.

We will also test whether CBT-I is superior to the waitlist control in preventing an insomnia diagnosis following treatment by using multiple logistic regression analysis.

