Hypotheses 1.2a and 1.2b are that individuals who were assigned to the CBT-I group will be less likely to have an insomnia diagnosis than those who were assigned to the waitlist control group at weeks 12 and 28. These hypotheses will be tested using 2 separate logistic regression models, one using the short-term (hypothesis 1.2a; 12 weeks) and one using long-term (hypothesis 1.2b; 28 weeks) follow-up insomnia diagnosis, as defined by the Duke, as the dependent variable, with treatment (CBT-I, waitlist) as the independent variable.

Statistical analyses aim 2 is to determine whether a brief, telehealth CBT-I improves well-being during the COVID-19 pandemic. We will test whether immediate CBT-I is superior to a waitlist control in improving depressive symptoms as the primary measure of well-being during the waitlist-controlled period (28-week duration) by using a mixed effects linear model with autoregressive error structure using intention-to-treat analysis. Depression severity, as assessed by the BDI-II, will be entered as the dependent variable with baseline covariates used for stratified randomization (ie, baseline insomnia severity and sex), group (immediate CBT-I or waitlist control), time point (weeks 0-6, 12, and 28), and group-by-time interaction included as fixed effects. The model will also include a random slope. Separate, secondary analyses will be conducted on the secondary measures relating to well-being described in the Secondary Outcomes section (eg, anxiety, suicidality, quality of life). Several hypotheses will be tested using this model.

Hypothesis 2.2a is that individuals assigned to the CBT-I group will have an improved trajectory of depressive symptoms across the 28 weeks relative to individuals assigned to the waitlist control group. This hypothesis will be tested using a likelihood ratio test of the coefficients of the time and group-by-time interaction terms of the aforementioned mixed effects linear model.

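### The Aim 3 models omit the week 0 outcome, so they show who ends up worse but not who worsens or who responds to treatment

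*Protocol article*

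**What the plan says.** In the protocol article, Primary Analyses, hypothesis 3 is that the risk factors "will collectively predict a worse long-term outcome across both intervention arms". The model is spelled out. Its response is the ISI or depression score at the two later follow-ups, weeks 12 and 28. Its predictors are also listed in full: "with social isolation, perceived stress, sleep reactivity, screen time, and physical activity measures at baseline as well as experimental arm entered as predictors". The week 0 ISI or depression score is neither a covariate nor a level of the response.

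The models for the other two aims do take in the starting level. Aim 1 has a time factor that includes week 0: "time point (weeks 0, 6, 12, and 28". Aim 2 also has week 0 in its time factor and names "baseline covariates used for stratified randomization (ie, baseline insomnia severity and sex" as fixed effects. The missing score is available: "Primary outcomes of insomnia, well-being, and predictors of treatment response are collected at baseline (week 0), weeks 6, 12, 28, and 56".

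The article describes the purpose of these models in more than one way:
- Objectives, opening paragraph: to identify pandemic-related risk factors for a worsening of well-being and sleep.
- Objectives, Aim 3: the factors "will predict worse long-term outcomes at 12 and 28 weeks across both study groups".
- Measures, under the heading Predictors of Treatment Response: the factors "are measured as predictors of long-term treatment outcomes".
- Discussion, first paragraph: the project examines pandemic-related predictors of response to the intervention.

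**The concern.** Worsening and response are both defined relative to where a participant started. A model of the follow-up level that leaves out the starting level mixes two things: the link between a factor and severity at entry, carried forward, and any prediction of what happens after entry.

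The link at entry is plausible on the article's own premise. Its Introduction treats loneliness, perceived stress and screen time as risk factors for insomnia and poor well-being, so they may well go with ISI and depression scores at week 0.

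At stake is the reading of Aim 3. A factor could be reported as a driver of worsening when it only marks those who entered with more symptoms. The article says its findings should guide later trials, so the misreading could be passed on. The treatment comparisons of Aims 1 and 2 are not affected.

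**Working it through.** **The plan's own figure.** The article gives no figure for Aim 3. Its one design figure, 80% power for d = 0.80 with 25 per group at 5%, is reproduced (80.7% by the normal approximation, 79.1% by the two-sided t test). It concerns the treatment contrast and has no bearing here.

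**Inputs.** From the article: five factors plus arm; response at weeks 12 and 28; 49 randomized; 34 with week 28 data at the time of writing; current ISI ≥10 required at entry. Assumed, because the article gives neither: r, the correlation of a factor with the baseline outcome (0.3 to 0.5), and b, the correlation of baseline with follow-up outcome (0.3 to 0.7).

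**One factor entered with arm.** Standardize, and let follow-up = b × baseline + arm effect + error, with no direct effect of the factor. Randomization makes the factor independent of arm.
- Without the baseline outcome, the factor's coefficient is cov(factor, follow-up) / var(factor) = r × b.
- With the baseline outcome, it is (rb − r × b) / (1 − r²) = 0.

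**Simulation.** 2000 runs per setting, five factors each correlating r with baseline and 0.3 with one another, arm effect 0.8 SD, no direct effect of any factor, and one regression on a single follow-up score as a simplification of the mixed model. The coefficients are for one factor entered with arm; the joint test covers all five.

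| r | b | r × b | Simulated coefficient, N=34 / N=49 | Joint test rejects, N=34 / N=49 |
|---|---|---|---|---|
| 0.3 | 0.3 | 0.09 | 0.087 / 0.090 | 7% / 9% |
| 0.3 | 0.5 | 0.15 | 0.145 / 0.151 | 13% / 17% |
| 0.3 | 0.7 | 0.21 | 0.203 / 0.207 | 22% / 33% |
| 0.5 | 0.3 | 0.15 | 0.150 / 0.153 | 12% / 17% |
| 0.5 | 0.5 | 0.25 | 0.251 / 0.247 | 32% / 49% |
| 0.5 | 0.7 | 0.35 | 0.352 / 0.348 | 68% / 87% |

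With the baseline outcome added, the coefficient lies between −0.005 and 0.004, and the joint test rejects in 4% to 6% of runs.

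**All five factors together.** The planned model enters the factors jointly, so they share the carried-forward link. With mutual correlation 0.3, each coefficient is r × b / (1 + 4 × 0.3) = r × b / 2.2, which is 0.09/2.2 = 0.04 to 0.35/2.2 = 0.16. Individual coefficients are therefore smaller than r × b, while the joint test picks up the sum.

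**Effect of the ISI entry rule.** Modelled as keeping only the upper half of a normal baseline, N=49, with r and b as they are before truncation. The baseline variance falls to 1 − 2/π = 0.363, and the single-factor coefficient becomes r × b × 0.363 / (1 − 0.637r²).
- r=0.3, b=0.5: 0.058 (simulated 0.058)
- r=0.5, b=0.5: 0.108 (simulated 0.109)
- r=0.5, b=0.7: 0.151 (simulated 0.145)

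The joint test then rejects in 7%, 12% and 26% of runs, against 4% to 5% with the baseline outcome added. The eligibility criteria set no cut-off on depression severity, so this attenuation cannot be claimed for the depression model in the same way.

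**The case against.** The strongest reply is that hypothesis 3, read literally, is about level. It speaks of a worse long-term outcome across both arms, and for the question of who ends up worse, a model without the baseline outcome is legitimate. That stands. The planned model is not wrong for that question, and it should be kept.

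A reader might go further and infer that hypothesis 3 has an inflated type I error of a known size, or that these factors are bound to appear predictive. The documents support neither. The rejection rates above are false-positive rates only under the null that a factor adds nothing beyond baseline severity, and hypothesis 3 states no such null. Under its literal wording the same associations are real and correctly detected. The rates also rest on two assumed correlations and a simplified model.

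A second reply is that adjustment has a price. All participants were required to have a pre-pandemic ISI below 10, and the article treats the risk factors as possible contributors to onset. Baseline severity may thus lie on the path from factor to outcome, and conditioning on it removes that part of the total association. This also stands, and it is the reason to report both models.

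A third reply is that the article puts estimation ahead of significance testing. This does not help, because the estimate itself mixes the two components.

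Finally, the treatment-response wording appears in headings and the Discussion and not in hypothesis 3. That is true, and it makes the relabelling a small matter. But the model has no factor-by-arm term, and the moderators named in Secondary Analyses are age and sex, so nothing planned would support the label.

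**Conclusion.** The point holds as a mismatch between the Aim 3 model and part of its stated purpose. It is a cheap improvement and not a proven error. The model as written answers a crude prognostic question; it cannot support statements about worsening or about treatment response.

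For a factor with no value beyond baseline, the carried-forward coefficient is 0.09 to 0.35 SD per SD when the factor is entered with arm, under the assumed correlations. It is smaller per factor when five correlated factors are entered together, and about 0.06 to 0.15 for ISI in the truncated scenarios. If a factor is unrelated to entry severity, or entry severity does not persist, there is nothing to correct.

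**What to change.** - Add the week 0 score of the outcome to each hypothesis 3 model: week 0 ISI in the ISI model, and in the depression model the week 0 score of whichever instrument is the outcome. That instrument should be named, because the article gives PHQ-9 as the primary depression measure but uses BDI-II in the Aim 2 model.
- Use the continuous score. The randomization stratum (ISI ≥10 or <10) will not serve, because eligibility requires ISI ≥10.
- Make the adjusted model the basis for any claim about worsening, and report the planned model beside it, labelled as crude prognosis. State that the two answer different questions because baseline severity may lie on the path from factor to outcome.
- Describe the results as prognostic, and drop the treatment-response label for these models.
- Record the choice before the hypothesis 3 models are fitted.

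The cost is one degree of freedom per model and a second set of estimates; no new data are needed. Adding sex is optional.

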Cognitive behavioral therapy for insomnia (CBT-I) is the gold standard, first-line, nonpharmacological treatment for chronic insomnia recommended by the American College of Physicians [24]. It has been proven safe and effective in adults across the lifespan, in individual [25] and group formats [26] and when delivered in person or via telehealth [27]. A recently published article [28] from the European Academy for CBT-I provided evidence supporting the efficacy of CBT-I to treat sudden-onset insomnia and the validity of telehealth-delivered CBT-I. There is evidence that CBT-I not only reduces sleep complaints in those with chronic insomnia but can also reduce depression, anxiety, and suicidality and improve quality of life [29-33]. There is further evidence demonstrating that the resulting improvements in insomnia symptoms mediate the changes in depression symptoms but not the reverse [34]. Although the literature on this is limited, taken together, this evidence suggests that providing a brief, telehealth-delivered CBT-I to individuals with newly developed, pandemic-onset insomnia complaints may not only improve sleep but also improve well-being. However, to our knowledge, there are no studies investigating whether CBT-I would be an effective early treatment for insomnia arising from a highly disruptive and stressful event, such as a global pandemic, or whether intervening early in insomnia symptom onset could help mitigate other negative mental health outcomes. Additionally, it remains unknown whether common risk factors (eg, loneliness, perceived stress, and screen time) for insomnia and poor well-being that have been exacerbated by the pandemic may impact the effectiveness of an early intervention for insomnia symptoms.

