#### Secondary Analyses

Secondary analyses will be conducted. (1) Analytic methods described in the primary aims will be repeated but applied to secondary measures of sleep disturbance and well-being outcomes as described in the Secondary Outcomes section. (2) Analytic methods described in the primary aims will be repeated but applied to outcome measures collected at week 56. (3) Sparse unsupervised clustering and principal component analysis analyses will be used to identify cohesive factors of dysfunction in sleep complaints and patterns of mental health outcomes at baseline. Regression models will be used to quantify the relationships within and between sleep complaints and patterns of mental health outcomes. (4) Age and sex differences in treatment response and as moderators of relationships between sleep complaints, insomnia risk factors, and mental health outcomes will be explored.

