## Discussion

Here, we outline the protocol of an innovative research project responding to the mental health crisis related to the COVID-19 pandemic. We aim to address several gaps in the literature by investigating the use of an early, brief, nonpharmacological insomnia intervention delivered via telehealth to treat insomnia symptoms arising during a stressful life event and prevent worsening insomnia or mental health outcomes. This study represents multiple levels of innovation. First, to the best of our knowledge, this is the only project clinically responding to the large-scale increase in sleep disturbance during the COVID-19 pandemic. Although many studies are documenting the robust changes in sleep during the pandemic, this project is the first to test an intervention and examine pandemic-related predictors of intervention response. Second, on a broader scale, this is one of only a few studies testing the prospective temporal relationship between sleep disturbance and well-being. Lastly, to our knowledge, this is the only study of early deployment of CBT-I to treat insomnia symptoms arising from a stressful global event.

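### The pooled model for the baseline risk markers suits Aim 3, which is prognostic, but with no marker-by-arm term it cannot support the treatment-response claims made for the same markers

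*Protocol article*

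**What the plan says.** The Protocol article describes the baseline risk markers in two ways.

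*As prognostic factors.* Under Objectives, Aim 3 hypothesizes that they "will predict worse long-term outcomes at 12 and 28 weeks across both study groups". Hypothesis 3, in Primary Analyses, is likewise framed over both arms. The model for it has social isolation, perceived stress, sleep reactivity, screen time and physical activity "measures at baseline as well as experimental arm entered as predictors". No interaction with arm is named.

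*As bearing on response to CBT-I.*
- Background lists as unknown whether such risk factors "may impact the effectiveness of an early intervention for insomnia symptoms".
- Primary Outcomes groups them with the outcomes: "Primary outcomes of insomnia, well-being, and predictors of treatment response are collected at baseline".
- The measures section headed Predictors of Treatment Response lists six markers (loneliness, sleep reactivity, perceived stress, screen time, social connection, physical activity) and says they "are measured as predictors of long-term treatment outcomes".
- Discussion claims as an innovation that "this project is the first to test an intervention and examine pandemic-related predictors of intervention response".

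The only treatment-response analysis by a baseline characteristic is item 4 of Secondary Analyses: "Age and sex differences in treatment response and as moderators of relationships". Items 1 and 2 there repeat the primary methods on other outcomes and on week 56.

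**The concern.** Whether a marker predicts outcome and whether it predicts benefit from treatment are different questions. The second is about how the difference between arms changes with the marker, so it needs a marker-by-arm term or an equivalent comparison of arm-specific slopes. The stated model has neither. In addition, the waitlist group gets no study treatment until after week 28 (Trial Design; Control Condition), so about half of the pooled data at weeks 12 and 28 come from untreated people. The coefficient is therefore not even a predictor of outcome among the treated.

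At stake is what the trial can conclude about who benefits. The article intends its results to guide larger trials and inform later hypotheses, and doubts that the study can be repeated. A prognostic marker read as a marker of response could send that later work in the wrong direction. Conversely, a marker whose slope with outcome is opposite in the two arms would look irrelevant.

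**Working it through.** **1. The plan's own figures.** None bears on marker effects. The one stated power figure (80% with 25 per group, d = 0.80, 5% level) is for the arm comparison. Taken as two-sided it reproduces: 80.7% by the normal approximation and 79.1% by the exact t test. It is not in dispute.

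**2. What the additive coefficient estimates.** Take one standardized marker with the same spread in both arms. Without an interaction term, its coefficient is approximately

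w × (CBT-I slope) + (1 − w) × (waitlist slope), with w the share of participants in CBT-I.

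With 26 and 23 randomized (Trial Status and Timeline), w = 26/49 = 0.53, close to one half. Define benefit as waitlist ISI minus CBT-I ISI. The change in benefit per SD of marker is then the waitlist slope minus the CBT-I slope. Illustrative slopes in ISI points per SD:

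| CBT-I slope | Waitlist slope | Pooled coefficient at 1:1 | Change in CBT-I benefit |
|---|---|---|---|
| +1 | +1 | +1 | 0 |
| 0 | +2 | +1 | +2 |
| +2 | 0 | +1 | −2 |

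At 26:23 the second and third rows become 0.47 × 2 = 0.94 and 0.53 × 2 = 1.06. The planned model cannot tell the three cases apart.

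**3. Check by simulation.** Settings: 4,000 trials per case, 50 participants, 1:1, one standardized marker, one time point, residual SD 1.

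| True slopes, waitlist / CBT-I | Mean additive coefficient | Mean marker-by-arm coefficient (CBT-I minus waitlist) |
|---|---|---|
| 0.4 / 0.4 | 0.40 | 0.00 |
| 0 / 0.8 | 0.40 | 0.80 |
| 0.8 / 0 | 0.40 | −0.80 |
| −0.4 / 0.4 | 0.00 | 0.80 |

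In the last case the additive model rejected in about 6% of trials, near its nominal 5%, although the slopes differ by 0.8. The interaction model recovered the true difference every time.

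**4. Precision if the term is added.** With a standardized marker and 1:1 arms, SE of the slope difference ≈ 2 × SD/√N. The residual ISI SD is not in the article; 4 to 6 is assumed. N = 37 is the number who had completed week 12, and also the week 28 number if the 3 awaited participants complete (34 + 3).

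- SD 4: 2 × 4/√37 = 1.32; half-width 1.96 × 1.32 = 2.6 ISI points per SD.
- SD 6: 2 × 6/√37 = 1.97; half-width 1.96 × 1.97 = 3.9 ISI points per SD.

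In residual-SD units (two-sided 5%, 80% power), the detectable slope difference is 0.79 at N = 50, 0.80 at N = 49 and 0.96 at N = 34. Power for a slope difference of 0.4 is 29%, 29% and 21%.

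**5. Does Secondary Analyses item 4 fill the gap?** No. Its treatment-response part covers age and sex only. Its other part makes age and sex, not arm, the moderators of relationships that involve the risk factors.

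**The case against.** The strongest reply is that the model does what the aim asks. Aim 3, hypothesis 3 and the opening statement of objectives are all prognostic, and baseline markers plus arm is a suitable model for them. The treatment-response language sits in a knowledge gap, a label, a heading and one Discussion phrase; none is an aim or a hypothesis. The sentence under the heading, on long-term treatment outcomes, can also be read prognostically. This stands, and it limits the point to a mismatch between model and claims.

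A reader might go further and infer that the Aim 3 analysis is wrong. The documents do not support that, since no stated hypothesis is tested with an unsuitable model. Nor do they support saying that the trial will report these coefficients as markers of response: the article does not say so, and the mislabelling is only a risk. Nor can one infer that no moderator analysis of the markers exists anywhere. Only the article is at hand, and a fuller plan may hold one. What can be said is that the model stated here does not support the claim stated here.

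It may also be said that the trial is too small for interactions. It is too small to test them. But Statistical Procedure and Data Analysis puts estimation and confidence intervals ahead of significance, and exploratory estimates with wide intervals are consistent with that.

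**Conclusion.** The point holds as a mismatch. The pooled model is right for the prognostic Aim 3 and should stay. It cannot support the treatment-response statements in Background, Primary Outcomes, Predictors of Treatment Response and Discussion, because its marker coefficient is roughly the average of the two arm slopes and is compatible with more, less or unchanged benefit from CBT-I. This follows from the model's form. It assumes near-equal arms, similar marker spread in each arm, and other markers that do not distort the picture. The slopes shown are illustrative, and the precision figures also depend on the assumed SD and on a single-marker, single-time-point approximation. Aims 1 and 2 are untouched. The change is worth making because it settles what the trial may say about who benefits, and it is cheap.

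**What to change.** Keep the Aim 3 model and report it as prognostic. Then do one of the following.

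- **Add exploratory models.** For each baseline marker and each outcome (insomnia severity, depressive symptoms), fit one model with a marker-by-arm term. Report the two arm-specific slopes and their difference with a 95% CI, and make no significance claim. Reserve the treatment-response label for that difference. Six markers are listed in the measures section and five are named in the model, so state how they correspond, in particular which measure represents social isolation.
- **Or change the wording.** Call the markers prognostic factors in Primary Outcomes, in the Predictors of Treatment Response section and in Discussion. State that the trial does not address the effect-modification question raised in Background.

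Cost: the first option is 6 × 2 = 12 short models (10 if only the five named markers are used) on data already collected, with the wide intervals shown above. The second option is an edit at three places plus one sentence.
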